### Intervention Group

#### Overview

The intervention group will receive usual care, plus a text message support program that includes a series of text messages focused on lifestyle modification for obesity prevention, as well as an opportunity to speak with an English-speaking health counselor over six months, as detailed below.

#### Message Content, Frequency, and Sequence

The text message content was co-designed with adolescents and research/health professionals and using established scientific methods [37]. The bank of 107 unique text messages are based on seven behavior change techniques with demonstrated effectiveness in adolescent obesity prevention interventions [38], and on evidence-based health information found in current national obesity prevention, nutrition, and physical activity guidelines [36,39,40]. Findings from previous text message development research with adolescents were also applied to ensure the text message style and language were appropriate and engaging for adolescents [31,32,41,42].

Each intervention participant will receive a customized and semipersonalized set of text messages sent on four random days per week, including one weekend day, and at random times (Table 1). Each unique text message will only be sent only once during the 6-months. If the participant is attending high school, the weekday text messages will only be sent before or after school hours (8:00 AM to 9:00 AM or 3:30 PM to 7:30 PM). Text messages are based on four priority areas, namely, healthy eating behaviors (n=26), physical activity behaviors (n=18), mental wellbeing (n=21), and general behaviors (n=34), and a total of 6 text messages prompt communication with the health counselor. One welcome message and one final text message are included in the bank of 107 text messages. General behavior messages are focused on the environmental impact of eating and activity, food environment, time management, and practical tips.

The text messages will be semipersonalized by using the participant's name and selecting text message content relevant to the participant's characteristics, such as age. Participants can also update their personal information (eg, mobile phone number or change in school attendance) throughout the study. Messages are sent at no cost to the participants; however, text message replies to the study team will be paid for by the participant at standard short message service (SMS) rates set by their mobile phone provider. The intervention will encourage two-way communication, with participants monitored by the health counselor on weekdays. All replies and responses will be reviewed in regular weekly team meetings.

**Table 1 table1:** Examples of text messages sent to the intervention group.

Text message category	Example text message
Introductory	*Hi [pref_name]^a^, welcome to the TEXTBITES^b^ study. We hope you find the program fun and helpful. If you have any questions throughout the program, text us or call. We are here to support you! If you ever want to stop the messages, respond STOP to opt-out.*
Physical activity	*Need a dose of some happy hormones? Stretching can release endorphins, reduce your stress and make you feel great. The best part? You can do it anywhere, even while watching TV or YouTube. Check it out: tinyurl.com/stretchyout.*
Nutrition	*Corn isn’t just a tasty snack, it’s multi-purpose! It can be used to make fireworks, glue, paint & plastic. But let's face it, popcorn is one of the best uses, check out some recipe ideas here: tinyurl.com/airpopcorn.*
Mental wellbeing	*Your brain has 86 billion thinking cells (called “neurons”) & 80 billion or so supporting cells. Wow, that's a lot! No wonder they need a break at night to rest & recover. Make sure to give them 8-10 hours rest each day!*
General behaviors	*Want to get your homework or study done in record time? Do power bursts! Put your phone on do not disturb and power it out for 25 min. Take a 5 min break (yep, you can check your phone) and repeat until your work is done!*
Health counselor	*How is everything going, [pref_name]? Text back if you would like to chat with our health counsellor about all things food, exercise and wellbeing and we will get back to you soon.*
Final	*This is your last message from the TEXTBITES study. Thank you for being a part of the program, we couldn’t have done it without you! We will contact you shortly to arrange your 6-month follow-up interview. Thanks again from the TEXTBITES study team!*

^a^pref_name: participants preferred first name

^b^TEXTBITES: TEXT message Behavioral Intervention for Teens on Eating, physical activity, and Social wellbeing

#### Role of the Health Counselor

Once a month, over six months, intervention participants will be sent a text message encouraging them to call the university-qualified health counselor to ask questions or request additional information (Table 1, example, two-way communication messages). The health counseling calls will employ complementary theoretical approaches to the text messages, including motivational interviewing, goal setting, self-monitoring, barrier identification, and problem-solving [43,44]. The personalized health counseling calls will last 10-15 minutes and will be delivered according to a standardized protocol. The university-qualified health counselor (allied health professional) will monitor and respond to participants’ request for a call each month, either via text message or phone call, within three working days. Participants are allowed a total of six health counseling calls in total over six months. The health counseling calls will enable participants to set behavioral goals, discuss barriers and enablers to behavior change, and their overall progress. This part of the intervention is based on the evidence based TEXTMEDS (TEXT messages to improve MEDication adherence and Secondary prevention) study for secondary prevention of heart disease [45].

### Text Message Management System

The text message management system was developed in conjunction with the text message intervention to support women's physical and mental health after breast cancer treatments study and has similar processes [46]. Each week messages will be selected from the message bank by the software sequencer system that ensures that participants are receiving the correct messages (intervention vs control). Both intervention and control groups will receive a welcome text message at the beginning of the study and a concluding message at the end of the 6-months. Each text message will have a unique signature to ensure that participants know these messages are from the TEXTBITES study. All participants will be given brief training at baseline on how to read, delete, and save a text message, and how to unsubscribe if required. Training will also include safe and acceptable times to read the text messages (eg, reminding participants they must not read the text messages or use any other mobile phone functions if they are driving). All participants will also be provided with the research personnel’s contact details and will be contacted at least once during the intervention period to organize the six-month follow-up assessment and once during the follow-up period to facilitate the twelve-month follow-up assessment.

A researcher will manage a study mobile phone, and a record will be kept of any incoming messages from participants, and all out-going replies from the study health counselor throughout the study. Any analysis of these incoming text messages will be performed at the group level, except for reporting examples of individual quotes, which will be anonymized to protect the participant’s identity. Participants from either group can withdraw from the study at any time with or without giving a reason by replying “STOP” to any of the messages or contacting a member of the research team, which will activate a process of review and withdrawal from the study. If a reason for withdrawal is provided, it will be recorded.

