### Control Group

The control group will receive usual care. For this study, usual care is defined as accessing available health services and information for adolescent obesity prevention, as outlined in the clinical practice guidelines for overweight and obese adults, adolescents, and children in Australia [36]. Participants in the control group will receive an initial text message welcoming them to the study. However, they will not receive the text message support program or health counseling telephone calls. The control group will also receive a text message reminder approximately six- and twelve-months after their enrolment, notifying them that they will be contacted to schedule their six- and twelve-month follow-up visits, respectively. Participants in the control group will be offered the opportunity to receive the text message support intervention (no health counseling) at the end of the study (twelve-month visit) if they wish.

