The primary analysis will include all available participant data and will be performed at the end of the study after all the data has been collected. The analysis of the primary and secondary outcomes will be conducted according to the intention-to-treat principle. Continuous outcomes will be analyzed at six- and twelve-months using analysis of covariance (ANCOVA), adjusting for baseline measurement of the outcome, gender, and recruitment site/strategy. Categorical outcomes will be analyzed at six- and twelve-months using log-binomial regression and adjusting for baseline measurement of the outcome, gender, and recruitment site/strategy. Planned subgroup analyses will investigate interactions between treatment and subgroups, including categories of age, socioeconomic status, and ethnicity, to explore trends for future studies. A significance level of 0.05 will be used. All analyses will be undertaken using SAS version 9.4 (SAS Institute Inc, Cary, North Carolina, United States).

Process evaluation data, including questionnaire data, interview data, and text message management data, will be analyzed using mixed methods. Descriptive analysis will be used to examine questionnaire data and software analytics. Interviews will be conducted by a trained qualitative interviewer, digitally recorded and transcribed. Interview data will be analyzed thematically, and coding based on emergent themes using the NVIVO Software program, version 12 (QRS International Pty Ltd, Victoria, Australia).

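### A STOP reply is presented to participants as ending the messages but starts withdrawal from the study, which risks selective loss of outcome data, mainly in the intervention arm

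*Protocol article*

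**What the plan says.** Two places in the article give the STOP reply different meanings.

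- **Message Content, Frequency, and Sequence, Table 1 (introductory message to the intervention group):** "If you ever want to stop the messages, respond STOP to opt-out". The participant is told that the reply ends the messages.
- **Text Message Management System:** "Participants from either group can withdraw from the study at any time with or without giving a reason", either by replying STOP to any message or by contacting the research team, "which will activate a process of review and withdrawal from the study". Here the reply starts an exit from the trial.

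The latter section also trains all participants in "how to unsubscribe if required", but names no separate keyword or procedure for leaving the messages alone. It says that all participants "will be contacted at least once during the intervention period to organize the six-month follow-up assessment", and does not say whether this still applies after a STOP reply.

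Under Statistical Considerations, the primary analysis uses all available data. Continuous outcomes are analysed by ANCOVA at six and twelve months, adjusted for the baseline value, gender and recruitment site or strategy. The stated principle is: "The analysis of the primary and secondary outcomes will be conducted according to the intention-to-treat principle".

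**The concern.** Stopping the intervention and stopping follow-up are different events. An intention-to-treat comparison needs outcomes from people who stop the intervention, because their results are part of the effect of offering it. As written, one text reply can set off both events, and the adolescent who sends it has been told about only the first.

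The trigger is also unevenly spread. The rule covers both groups, but the intervention group receives a long series of messages and controls receive very few. Tiring of the programme is a reason to reply STOP that exists almost entirely in one arm. If the review usually ends in withdrawal, the missing six- and twelve-month BMI z scores would come mainly from the intervention participants least engaged with the programme. The available-data ANCOVA would then compare those who persisted with a less selected control group. The planned baseline comparison of completers and noncompleters can describe such loss but cannot correct it, and it cannot show how those lost would have responded.

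**Working it through.** **1. Exposure to the trigger.** "The bank of 107 unique text messages" is made up of 26 + 18 + 21 + 34 + 6 = 105 programme messages, plus one welcome and one final message, giving 107. The Control Group section says of controls that "they will not receive the text message support program or health counseling telephone calls". That section and Text Message Management System give them a welcome message, a concluding message and reminders at about six and twelve months, so about four.

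**2. The plan's own sample size.** Inputs from Statistical Considerations: difference 0.15, SD 0.27, two-sided 5% type I error, 80% power, 1:1 allocation, 30% dropout.

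- Normal approximation: n = 2 × (1.960 + 0.842)² × 0.27² / 0.15² = 50.9, so 51 per arm. 51 / 0.70 = 72.9, so 73 per arm and 146 in total.
- Two-sample t test: 51.84, so 52 per arm. 52 / 0.70 = 74.3, so 75 per arm and 150 in total.

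The stated 150 is reproduced. The 30% is a single figure with no split by arm.

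**3. Possible bias.** Let s be the share of the intervention arm lost through STOP. Let g be the amount by which their mean BMI z score change is worse than that of those who stay, given the covariates. Suppose everyone else is observed. The true intervention-arm mean is (1 − s) × stayers + s × stoppers, and the available data give the stayers' mean alone. The benefit is therefore overstated by s × g. The article gives neither s nor g, so both are assumptions. Percentages are of the 0.15 target.

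| s | g = 0.05 | g = 0.10 | g = 0.15 |
|---|---|---|---|
| 5% | 0.0025 (1.7%) | 0.005 (3.3%) | 0.0075 (5.0%) |
| 10% | 0.005 (3.3%) | 0.010 (6.7%) | 0.015 (10.0%) |
| 20% | 0.010 (6.7%) | 0.020 (13.3%) | 0.030 (20.0%) |
| 30% | 0.015 (10.0%) | 0.030 (20.0%) | 0.045 (30.0%) |

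If g = 0, the bias is zero whatever the STOP rate.

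**4. Possible loss of power.** Suppose STOP withdrawals come on top of the planned 30%, in the intervention arm only. Then n(intervention) = 75 × (0.70 − s), n(control) = 52.5, SE = 0.27 × √(1/n(intervention) + 1/n(control)), and power = Φ(0.15/SE − 1.96).

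| Extra loss | n(intervention) | Power |
|---|---|---|
| none | 52.5 | 81% |
| 5 points | 48.75 | 80% |
| 10 points | 45 | 78% |
| 20 points | 37.5 | 74% |
| 30 points | 30 | 68% |

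If the withdrawals fall inside the 30%, power is as planned. The allowance protects numbers, not comparability.

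**The case against.** The strongest reply is that the article nowhere says outcome data are discarded or visits refused after STOP. The reply starts a review as well as a withdrawal, and the review is not described. All participants are to be contacted about the six-month visit, with no exception stated. Unsubscribe training is compatible with a message-only exit. The article is a condensed account of a protocol (Version 2.0) that is not shown and may separate the two acts. Handling of missing data commonly belongs in an analysis plan, also not shown. Most of this stands, and it limits what can be claimed.

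A reader might infer several stronger things that the article does not support:

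- **That data are lost automatically.** The review step leaves this open.
- **That loss falls on the intervention arm only, with nearly all controls retained.** The rule covers either group, and the dropout figure is not split by arm. Mainly is as far as the message counts go.
- **That the comparison is biased and is not intention-to-treat.** Bias needs an appreciable STOP rate, loss of follow-up after the review, and stoppers who differ from stayers after adjustment. The stated principle is intention-to-treat; the problem would be missing outcomes.
- **That the effect is overstated by 11% to 43%.** Those figures follow if stayers gain 0.15, every stopper gains nothing and goes unmeasured, and 10% to 30% stop: 0.015/0.135 = 11% and 0.045/0.105 = 43%, relative to the true effect. That is close to a worst case.
- **That the 30% allowance is used up.** It covers dropout in general, which includes these withdrawals.

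The objection does not remove the conflict. The article states the rule itself, the stated end of the process is withdrawal from the study, and the participant was told something else.

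**Conclusion.** The point holds as a conflict between the Table 1 welcome message and Text Message Management System that creates a risk of selective loss. It does not show that bias will occur. The risk lies mainly in the intervention arm because of the exposure gap of about 107 messages to about four.

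The overstatement is 0.0025 to 0.045 BMI z score units, 2% to 30% of the 0.15 target. This assumes 5% to 30% of that arm lost through STOP, a gap of 0.05 to 0.15 between stoppers and stayers, and no other loss. It is zero if the two have the same expected change given the covariates. Any loss of power is secondary, and arises only if these withdrawals exceed the planned 30%.

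This should be fixed: measurements that are never taken cannot be recovered at analysis, and the change is small.

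**What to change.** Reconcile the two passages along these lines:

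- A STOP reply ends the messages, as the participant was told, and does not by itself end study participation.
- People who reply STOP are still offered the six- and twelve-month assessments and are analysed in their randomised arm.
- Withdrawal from follow-up is recorded separately, with its own code and date, and only when the participant or parent asks for it. The right to withdraw at any time without giving a reason is unchanged.
- The text says what the review after STOP consists of.

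The cost is a wording amendment to the protocol, participant information and STOP script, and one database field. The amendment may need ethics review. The abstract reports recruitment as already open, so enrolled participants may also need to be told. Some people contacted after STOP will decline the visit, so the change reduces selective loss without removing it.

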### Data Collection and Study Outcomes

The in-person follow-up assessments will occur at the end of the six-month intervention period and the end of the six months post-intervention (twelve months from baseline). The primary outcome, secondary outcomes, and their assessments are presented in Table 2. The primary outcome is a change in BMI *z* score (units BMI is above or below average for age- and sex-specific reference values) measured using calibrated stadiometer and electronic scales. BMI is calculated as weight (kg)/[height (meters)^2^]. Bodyweight and height will be measured to the nearest 0.1 kilogram and 0.1 centimeter, respectively, at each assessment time point by the research assistant, who is blinded to participant allocation and is using a standardized protocol [47]. Waist-to-height ratio will be measured to the nearest 0.1 centimeter using a nonstretch plastic waist measurement tape, midway between the iliac crest and the lowest rib, and a calibrated stadiometer.

**Table 2 table2:** Description of TEXTBITES study outcomes and assessments.

Outcome		Assessment
**Primary outcome**		
	BMI^a^* z* score	Units BMI is above or below average for the age- and sex-specific reference values measured using calibrated stadiometer and electronic scales [47].
**Secondary outcomes**		
	Waist-to-height ratio	The midway measurement between the iliac crest and lowest rib and height, measured using a non-stretch plastic waist tape and a calibrated stadiometer [47].
	Adherence to dietary guidelines	Short questions adapted from the New South Wales Population Health Survey [48]
	Diet quality, food choices and food patterns	ACAES^b^ Survey [49]
	Physical activity	Validated short physical activity question and study-specific sports participation questions [50]
	Sedentary activity	Modified ASAQ^c^ [51-53]
	Objective physical activity	Actigraph GT3X+ activity monitors worn for seven days [54,55]
	Sleep quality	PSQI^d^-Short [56,57]
	Quality of life	PedsQL^e^ Version 4.0 Generic Core Scales questionnaire [58]
	Self-esteem	Rosenberg Self-Esteem Scale [58]
	Self-efficacy	Short questions adapted from the Project Eat Survey II [59]
	Social support	Short questions adapted the social support and eating habits survey [60] and Social Support Scale for Physical Activity [61]
	Eating disorders	EDE-Q^f^ [62]
	Depression	CESDR-10^g^ [63]

^a^BMI: body mass index

^b^ACAES: Australian Child and Adolescent Eating Survey

^c^ASAQ: Adolescent Sedentary Activity Questionnaire

^d^PSQI: Pittsburgh Sleep Quality Index

^e^PedsQL: Pediatric Quality of Life Inventory

^f^EDE-Q: Eating Disorder Examination questionnaire

^g^CESDR-10: Centre for Epidemiological Studies Depression Scale-Revised-10

**Enrolment**										
	Eligibility screen	✓								
	Informed consent	✓								
	Allocation			✓						
**Interventions**										
	Intervention group					✓		✓		
	Control group					✓		✓		
**Assessments**										
	BMI^a^* z* score					✓		✓		✓
	Waist-to-height ratio					✓		✓		✓
	Adherence to dietary guidelines					✓		✓		✓
	Diet quality, food choices and food patterns					✓		✓		
	Physical activity					✓		✓		✓
	Sedentary activity					✓		✓		✓
	Objective physical activity					✓		✓		✓
	Sleep quality					✓		✓		✓
	Quality of life					✓		✓		✓
	Self-esteem					✓		✓		✓
	Self-efficacy					✓		✓		✓
	Social support					✓		✓		✓
	Eating disorders					✓		✓		✓
	Depression					✓		✓		✓

^a^BMI: body mass index

### Process Measures

The adolescents’ acceptability, utility, and engagement with the two-way semipersonalized text message intervention and interaction with a health counselor will be measured using a study-specific, process evaluation questionnaire, and semistructured telephone interviews. All intervention participants will be asked to complete the process evaluation questionnaire at their 6-month follow-up assessment. The questionnaire will include questions regarding acceptability and utility that require Likert responses from strongly agree to strongly disagree. It also includes open-ended questions about the most useful and least useful components of the program, as well as suggestions to improve the program. Measures of engagement with the program will be extracted from the text message management system, including the number of text messages sent and replies received. At the 6-month follow-up, both control and intervention participants will be asked if they accessed any other health-related information or programs regarding weight management or lifestyle behavior change. Intervention participants will be invited in person, or by telephone, to take part in a semistructured telephone interview at six-months. A minimum of 15 interviews will be conducted and will be consecutive until no new themes or categories emerge (thematic saturation). However, it is anticipated that at least 30-40 participants will be invited to take part. These interviews will be conducted by telephone and will last approximately 30 minutes. Participants will be purposively selected to ensure that a variety of views are explored and to obtain a mix of participants in terms of age and ethnicity.

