Despite the apparent risk for weight gain during adolescence, evidence to inform effective interventions for this population is lacking. A 2019 Cochrane review of 31 randomized controlled trials (RCTs) testing the effectiveness of a range of interventions, which included diet or physical activity components or both, designed to prevent obesity in adolescents found limited effective interventions for adolescents aged 13-18 years old [22]. There has been more investment in childhood obesity prevention research, with over 85 RCTs conducted in children aged 6-12 years old. Moreover, the diet and physical activity strategies delivered to adolescents in the studies did not reduce their body mass index (BMI) *z* score, and there has been limited investigation of digital intervention modalities. Current attrition rates for traditional, in-person obesity prevention and management interventions in adolescents remain highly variable, with 27% to 73% of participants dropping out of interventions for reasons including the intervention not meeting the adolescent’s expectations [23,24]. Digital technology has been identified as an engaging intervention modality for overweight and obese adolescents [25]. Thus, mobile phone interventions hold promise for delivering interventions that are scalable, low-cost, and engaging.

Currently, over 90% of adolescents living in Australia and the United States own a mobile phone [26,27], and text messaging remains a primary means of communication between adolescents [27]. There is a small body of evidence which indicates one-way text message interventions can promote weight loss in adults [28]. Emerging research has shown that text messages are a feasible and acceptable form of communication in interventions for adolescents with obesity [29-32]. However, there is limited high-quality evidence for the role of two-way text messages to improve obesity prevention behaviors in adolescents who are overweight. Therefore, the primary aim of this study is to test the effectiveness of a two-way, semipersonalized text message program, with optional health counseling, compared to usual care for improving adolescents’ BMI *z* score. This study also aims to determine if the text message program can improve lifestyle outcomes. The study will also examine acceptability, utility, and engagement with the program.

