### Statistical Considerations

Modest reductions in BMI *z* score (0.01-0.15) in adolescents have been associated with improvements in several cardiovascular risk factors and are considered to be clinically meaningful [64]. The population SD for this power calculation was obtained from a contemporary Australian RCT in adolescents [65]. To test for a change in BMI *z* score of 0.15 (SD 0.27) [65] in the intervention group at six-months, compared with the control group, for 80% power (type I error=5%, two-sided test), 1:1 randomization, and accounting for a conservative 30% dropout-rate based on a recent systematic literature review [66], we will require 150 participates (75 participants per group).

Baseline demographic characteristics, attrition rates, and the average number of text messages sent and received for participants will be tabulated and compared using descriptive statistics. Categorical variables will be summarized using totals numbers and percentages. Continuous variables will be summarized using mean and standard deviation for normally distributed data, or median and interquartile range for data that are not normally distributed. The baseline characteristics of completers and noncompleters will be compared to examine attrition bias, using two-tailed *t* tests for continuous variables and chi-square tests for categorical variables. Actigraph GT3X+ accelerometer data will be captured in 1-15 second epochs to capture the intermittent activity patterns of adolescents and downloaded using the ActiLife software into an excel spreadsheet. Time spent in different physical activities will be evaluated by classifying the intensity level using count thresholds specific to adolescents [54,55].

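### The acceptability and utility questionnaire has no stated route to intervention participants who miss the 6-month visit or stop the messages, so its ratings are likely, though not shown, to be too favourable

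*Protocol article*

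**What the plan says.** All references are to the protocol article.

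- **Questionnaire.** Process Measures: "All intervention participants will be asked to complete the process evaluation questionnaire at their 6-month follow-up assessment". It holds the Likert items on acceptability and utility, plus open questions.
- **Setting.** Data Collection and Study Outcomes: "The in-person follow-up assessments will occur at the end of the six-month intervention period". The occasion on which the questionnaire is given is therefore a physical visit.
- **Interviews.** Process Measures: "Intervention participants will be invited in person, or by telephone, to take part in a semistructured telephone interview at six-months". On selection: "Participants will be purposively selected to ensure that a variety of views are explored and to obtain a mix of participants in terms of age"; the same sentence also names ethnicity. On number: "A minimum of 15 interviews will be conducted and will be consecutive until no new themes or categories emerge (thematic saturation".
- **Stopping.** Text Message Management System: replying STOP to any message starts a review and withdrawal from the study. A reason is recorded only if one is given.
- **Engagement.** Process Measures takes counts of messages sent and replies received from the message system. The Abstract adds analysis of the health counselor logs. Neither source depends on attending a visit.
- **Dropout.** Statistical Considerations sets the sample size "accounting for a conservative 30% dropout-rate". The planned attrition check compares completers and noncompleters on baseline characteristics only.

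**The concern.** Acceptability, utility and engagement are stated aims, and the Discussion relies on the process evaluation to identify barriers and enablers to wider use. The questionnaire reaches a participant through a visit that some will not attend. One way of leaving the study, replying STOP, is also the natural response of someone who dislikes the messages. Non-response may therefore depend on the opinion being measured.

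The planned attrition check cannot reveal this, because baseline characteristics do not show what a leaver thought of the program. Interviews could fill part of the gap, but no stated criterion directs them to low engagers or to those who stopped. What is at stake is an acceptability figure that mostly reflects those who stayed, and a thinner record of why others left.

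**Working it through.** **1. The plan's own figure.** Inputs from Statistical Considerations: difference 0.15, SD 0.27, two-sided 5% error, 80% power, 1:1 allocation, 30% dropout.

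- Normal approximation: 2 x (1.96 + 0.84)² x 0.27² / 0.15² gives 51 per group. 51 / 0.70 = 72.9, so 73 per group and 146 in total.
- t distribution: 51.8, so 52 per group. 52 / 0.70 = 74.3, so 75 per group and 150 in total.

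The stated 150 (75 per group) reproduces. The 30% is thus the plan's own allowance for participants without a six-month outcome. I apply it to the intervention arm and to questionnaire non-response, which is an assumption.

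**2. Questionnaire respondents.** 75 x 0.70 = 52.5 attend and 75 x 0.30 = 22.5 do not. About 22-23 adolescents give no questionnaire data.

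**3. What can be said without assuming their views.** If a proportion p of attenders find the program acceptable, the whole-arm value lies between 0.70p (no non-attender agrees) and 0.70p + 0.30 (all agree).

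- p = 0.80: 0.56 to 0.86.
- p = 0.90: 0.63 to 0.93.

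The band is 30 points wide whatever p is.

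**4. Bias of the attenders-only figure.** Let a be the rate in attenders and b the rate in non-attenders. The whole-arm rate is 0.70a + 0.30b, so the bias is a - (0.70a + 0.30b) = 0.30 x (a - b).

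| Assumed difference a - b (points) | Bias (points) |
|---|---|
| 0 | 0 |
| 10 | 3 |
| 20 | 6 |
| 30 | 9 |
| 50 | 15 |

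The article gives no acceptability rate for either group, so every row is an assumption.

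**5. Would using all 75 as the denominator repair it?** Take an assumed 90% in attenders and 40-70% in non-attenders.

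- Whole arm: 0.70 x 0.90 + 0.30 x 0.40 = 0.75, and 0.70 x 0.90 + 0.30 x 0.70 = 0.84.
- Attenders only: 0.90, too high by 6 to 15 points.
- All 75 as denominator, with only attenders answering: 0.70 x 0.90 = 0.63, too low by 12 to 21 points.

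Counting silence as a negative view would replace one bias with a larger one in this example.

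**The case against.** The best defence has four parts.

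- **Interviews.** They also address acceptability and utility, are held by telephone, may be arranged by telephone, and are not restricted to attenders. Their first stated criterion is a variety of views. This stands. A reader might infer that acceptability is measured only in attenders, or that interviewees are varied by age and ethnicity alone; the text supports neither. What remains is that nothing stated turns variety of views into recruitment of low engagers or leavers, although the study's message records can identify both.
- **Evidence on why people leave.** The Introduction's "27% to 73% of participants dropping out of interventions for reasons including the intervention not meeting the" adolescent's expectations describes traditional in-person programs, which the article contrasts with digital ones. This also stands. It cannot be read as evidence that dropout here will reflect dislike of the messages; the burden of a face-to-face visit is an equally possible cause. The plausible direction of bias rests mainly on the STOP route.
- **Leavers are partly heard.** Volunteered withdrawal reasons, incoming messages and counselor logs are kept. That is true and useful, but none of them is a systematic rating of acceptability or utility.
- **The full protocol is not shown** and may contain a fallback for missed visits. That is possible, and it is one reason to rate the point low. Still, the article does more than stay silent: it fixes when and where the questionnaire is given.

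**Conclusion.** The point holds as a minor one. Followed as written, the article's only quantitative measure of acceptability and utility would miss about 22-23 of 75 intervention participants at the planned dropout. Those who disliked the messages are plausibly over-represented among them.

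The overestimate is 0 to 15 points if attenders and non-attenders differ by 0 to 50 points. That range is assumed, and the bias is zero if the groups do not differ. A reader might conclude that the acceptability results are biased upward as a matter of fact; the article supports only that this is likely.

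The data are descriptive, with no hypothesis test on acceptability. The engagement counts and the primary outcome are untouched.

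**What to change.** 1. At 6 months, send the questionnaire as an online link by text or email to every participant randomised to intervention who has not withdrawn consent to contact, whether or not the visit is attended.
2. Offer the same link at opt-out to those who stop the messages. Report these answers separately, because length of exposure differs.
3. Add engagement level (replies, calls) and early stopping to the purposive interview criteria, alongside variety of views, age and ethnicity.
4. Report acceptability and utility among responders, with the response rate out of all randomised to intervention and a best/worst-case range for non-responders. Do not use all 75 as the denominator of a single figure.

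**Cost.** Protocol wording and one extra link. The outcome questionnaires are already completed online and the interviews are already by telephone, so no visits are added. The downsides are a probably low response among leavers and a possibly less favourable figure.
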